## 3.2 Study design

This study is a single-center, prospective, single-blind, randomized, controlled trial. It aims to assess the efficacy of VR as a more effective preparation method for in-person simulation trainings, compared to e-learning. The focus is on improving physicians' trauma CPR management skills.

All recruited participants will watch a 60-minute video to learn about the requirements, steps, and other important information about this study. Furthermore, this introductory video will give an overview of management strategies for trauma patients going into cardiac arrest in an in-hospital setting and provides links to the guidelines (30–32) on which this study is based. It also indicates that knowledge of the content of the guidelines is a prerequisite for Phases 2 through 3. This video can be viewed as often as desired throughout the study. Participants will also be required to complete the electronic Questionnaire 1 (Additional file #2) prior to randomization, which assesses participants' baseline characteristics (including the German versions of the "Openness to Experience" subscale of the 100-item HEXACO-PI-R test (33,34) and the Technology Readiness Scale (35)).

Each participant will then complete either the e-learning course (control group) or the VR training simulations (intervention group) over a two-week period, both focusing on the same content. Both groups will spend approximately the same amount of time learning the same content, which will prepare the participants for the assessment in the simulation session. If participants do not complete the entire e-learning course or all four VR simulations, they will be dropped from the study.

After Phase 2, all participants will attend the simulation session and will be evaluated in the role of medical team leader of a standardized TCA scenario (Phase 3).

In addition, each participant will be required to complete Questionnaire 2 (Additional file #3) immediately following the simulation session in Phase 3. Only the intervention group will be required to complete the VR system usability portion of this questionnaire. The system usability scale (SUS) (36,37) will be translated and used in German.

[figure not shown]

**Figure 1.** The course of events during the study.

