### 3.2.2 Control and Intervention

The control group will complete an e-learning course over a two-week period in preparation for the subsequent simulation session, which will teach the same content as the VR simulation software in the intervention group.

Both e-learning and VR have the limitation that manual skills cannot be practiced. The content will therefore focus on procedural processes and guideline adherence in the context of trauma patient care and traumatic cardiac arrest in shock rooms. In addition to basic life support (BLS) and ALS, there will be additional specific learning content (15) such as structured patient assessment (xABCDE approach) and special care strategies for this unique patient population.

The e-learning course will also focus on basic principles of crew resource management (CRM) and related communication skills (15,39), such as closed-loop communication. It has also been shown that cognitive aids such as checklists, flowcharts, or mnemonics can be very helpful to HCPs in such settings, and their use is recommended (20). Accordingly, their use will also be an essential part of this e-learning course.

Once enrolled, all participants randomized to this group will receive access information for the course, which, like the VR training, will be conducted in German and must be completed within 2 weeks.

Participants randomized to the intervention group will learn and practice the exact same content using a VR training environment co-developed by the research team of this study. The developed software with its four TCA scenarios must also be practiced over a period of 2 weeks, which corresponds to the same time and learning effort as the e-learning course.

In order to make the VR training sessions as efficient as possible, it is necessary to provide the participants with an additional orientation module that must be played before the VR training sessions begin. This additional module will take about 20 minutes to play once to familiarize the participants with the technical features of the VR headset and the controllers and to keep their focus on the medical content instead of the technical features. The developed software will be a single-user application with automated agents as a resuscitation team for interaction.

All four virtual intervention group simulations or the entire e-learning course must be completed before entering Phase 3, or the participant will be dropped from the study.

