### **VR-related adverse events:**

AEs may occur during the use of VR, especially cybersickness (41). The following symptoms' incidence will be evaluated accordingly:

- Nausea and/or vomiting
- Dizziness
- Headaches
- Eye strain and fatigue (discomfort, blurred vision, reduced visual acuity)
- Physical effects (tripping, falling, and bumping into objects in the real world)

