*CPR = cardiopulmonary resuscitation, eFAST = extended focused assessment with sonography for trauma, POCUS = point-of-care ultrasound*

Table 2 provides a comprehensive list of items that are deemed protocol deviations until the necessary action is explicitly carried out or verbally communicated in its entirety. For an action or order to be considered timely in this context, it must be completed within the corresponding chronological category outlined in Table 2, which includes Primary Assessment → Secondary Assessment → Advanced Life Support. It is important to note that these determinations are made by an expert in the field, relying on their professional judgment. Each protocol deviation can only be committed once. Actions ordered or performed by the team leader are considered equivalent in this regard.

It should also be noted that all orders and actions can be successfully completed on the first attempt to further standardize the scenario in the setting of this study.

After each scenario, a standardized full-team debriefing will be conducted, focusing on critical actions and protocol deviations. Questionnaire 2 will also need to be filled in by each participant at this point in the study.

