| Learning method (participants' impression)                                     |                 |                      |
| - Learning progress                                                            |                 |                      |

|                                                           |                  |                      |
|-----------------------------------------------------------|------------------|----------------------|
| - Level of frustration                                    | Questionnaire 2  | 5-point Likert scale |
| - Level of enjoyment                                      |                  |                      |
| Participants' confidence in management of TCA             | Questionnaires 2 | 5-point Likert scale |
| Participants' performance                                 |                  |                      |
| - Participants' subjective impression                     | Questionnaires 2 | 5-point Likert scale |
| - Experts' impression                                     | Scoring sheet    | 5-point Likert scale |
| VR-related adverse events                                 | Questionnaire 2  | Incidence rate       |
| SUS                                                       | Questionnaire 2  |                      |
| - SUS score                                               |                  | 1 to 100             |
| - Adjective rating scale                                  |                  | 7-point Likert scale |
| Drop-out variables                                 |                  |                      |
| Training/studying with other non-study learning resources | Questionnaire 2  | Yes/no               |
| Insufficient preparation with assigned learning method    |                  | Yes/no               |

---

*ALS = advanced life support; AOI = area of interest; ATLS = advanced trauma life support; CPR = cardiopulmonary resuscitation; ERC = European Resuscitation Council; ETC = European Trauma Course; NASA-TLX = National Aeronautics and Space Administration Task Load Index; PHTLS = prehospital trauma life support; SUS = system usability scale; TCA = traumatic cardiac arrest; VR = virtual reality*

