### 4.3 Ethical considerations and risk-benefit-evaluation

Since this is a comparative study of different learning methods, there is no risk to the study participants. The only risk is the disclosure of sensitive information about them, which is minimized by pseudonymization and access restrictions.

Further hypotheses can be generated from the results of this study.

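### VR-related adverse events are asked about only after Phase 3, so participants who permanently stop VR because of symptoms are not asked, and the reported incidence can be understated

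*Protocol*

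**What the plan says.** All references are to the Protocol.

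- **Objective.** Section 2.3, item 10, makes the incidence of VR-related adverse events a secondary objective. Section 3.5 reports it descriptively and treats all secondary objectives as exploratory.
- **Expected events.** The adverse event paragraph in 3.2.2 expects events during VR use. It lists nausea or vomiting, dizziness, headache, eye strain, and physical effects such as tripping, falling and bumping into objects.
- **Source.** The row in Table 3 (3.4.1) reads "VR-related adverse events | Questionnaire 2 | Incidence rate". Section 3.4 names the two questionnaires and the scoring sheets as the data sources. No adverse event log or exit form is described.
- **Timing.** Section 3.2: "each participant will be required to complete Questionnaire 2 (Additional file #3) immediately following the simulation session in Phase 3". Section 3.2.3, after describing the debriefing: "Questionnaire 2 will also need to be filled in by each participant at this point in the study".
- **Drop-out.** Section 3.2: "If participants do not complete the entire e-learning course or all four VR simulations, they will be dropped from the study". Section 3.2.2 says the four VR simulations or the e-learning course "must be completed before entering Phase 3, or the participant will be dropped from the study". Section 3.1.3 lists incomplete preparation as a ground for withdrawal.
- **Risk statement.** Section 4.3 says that "there is no risk to the study participants" and names disclosure of sensitive information as the only risk.

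**The concern.** Whether a participant is asked about adverse events depends on having finished VR, and finishing VR can depend on having had an adverse event. Those whose symptoms were bad enough to end VR for good are missing from the only place where symptoms are recorded.

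At stake is secondary objective 10, the only safety result the trial plans. A figure from completers alone could make VR look better tolerated than it was. This is fixed by the time of data collection and is not an analysis detail that a statistical analysis plan could settle, because no later analysis can restore answers that were never sought. Section 3.5 also excludes observations with a missing primary outcome from the statistical analyses. Read literally, an event noticed informally in someone who never reached Phase 3 has no stated way into the results.

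**Working it through.** **Step 1: follow one participant through the plan.** VR takes place in Phase 2, over two weeks (3.2, 3.2.2). A participant stops because of symptoms and does not finish all four simulations. Sections 3.1.3, 3.2 and 3.2.2 then drop this participant before Phase 3. Questionnaire 2 follows the Phase 3 simulation (3.2, 3.2.3), so the participant does not receive it. A study team member is present in Phase 2 (3.6.1), but the stated purpose is technical help, with no mention of recording symptoms.

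**Step 2: reproduce the plan's own drop-out figure.** Section 3.3 needs 30 per group, 60 in all, and expects 10% drop-out. 60 / (1 − 0.10) = 66.7, rounded up to 67, as stated. The allowance is 67 − 60 = 7 participants, or 7 / 2 = 3.5 per arm: 3 to 4 in the VR arm for all causes together. With equal allocation (3.2.1) the VR arm has 33 or 34 participants.

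**Step 3: direction.** Let n start VR, x of them have an adverse event, and k of those x stop permanently because of it. Assume no other loss.

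- Incidence among all starters: x / n
- Incidence among completers: (x − k) / (n − k)
- Difference: x/n − (x − k)/(n − k) = k(n − x) / [n(n − k)]

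The difference is zero when k = 0 and is never negative. By this route the completers-only figure can be too low but not too high.

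**Step 4: size, under stated assumptions.** The Protocol gives neither x nor k. Assume n = 33 and x = 10, so x/n = 10/33 = 30.3%.

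| Symptom-related discontinuations (k) | Completers only | Shortfall, percentage points |
|---|---|---|
| 0 | 10/33 = 30.3% | 0 |
| 1 | 9/32 = 28.1% | 2.2 |
| 2 | 8/31 = 25.8% | 4.5 |
| 3 | 7/30 = 23.3% | 7.0 |
| 4 | 6/29 = 20.7% | 9.6 |

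The last two rows use up the VR arm's entire share of the planned drop-out.

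**Step 5: does the assumed rate drive this?** Start from what Questionnaire 2 would show, with 34 in the VR arm.

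- No event among completers: 0% reported, against 1/34 = 2.9% for k = 1, 3/34 = 8.8% for k = 3 and 4/34 = 11.8% for k = 4.
- About 10% among completers: 3/31 = 9.7% against 6/34 = 17.6% for k = 3; 3/30 = 10.0% against 7/34 = 20.6% for k = 4.
- About 20% among completers: 6/31 = 19.4% against 9/34 = 26.5% for k = 3.

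With 3 to 4 symptom-related discontinuations the shortfall is about 7 to 12 points across these rates; with none it is zero.

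**Step 6: two passages that do not fit together.** Table 3 lists insufficient preparation with the assigned method as a drop-out variable. Its source cell is empty, and the row above names Questionnaire 2, so the two rows appear to share that source. If so, some under-prepared participants would fill in Questionnaire 2, whereas 3.2.2 drops them before Phase 3. Separately, 4.3 denies any risk other than disclosure of data, while 3.2.2 lists vomiting and falls.

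**The case against.** The strongest reply is that the gap may be small or empty. Participants have two weeks for four simulations, and nothing bars someone who breaks off a session from finishing later and reporting the symptom in Questionnaire 2. Section 3.1.2 excludes people predisposed to cybersickness. The Table 3 drop-out item hints that some incompletely prepared participants may see Questionnaire 2 after all. The outcome is exploratory and descriptive, and usability, frustration and enjoyment are measured separately. The choice of denominator is commonly left to a statistical analysis plan.

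Most of this limits the size and weight of the point and stands to that extent. It does not remove the gap: no text provides for asking about symptoms in someone who stops for good in Phase 2, and a denominator of all starters is of little use without data on those who stopped.

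A reader might infer more than the Protocol supports:

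- *Anyone who stops VR is lost, so the worst cases are missing.* Only participants who never complete all four simulations are dropped, and the Protocol does not say that any will do so because of symptoms.
- *Discontinuation due to adverse events is recorded as zero.* It is not recorded at all. The participants would still be visible as drop-outs, without the reason.
- *The incidence will be about a third too low.* That describes k = 4 (20.7% against 30.3%), which attributes essentially all planned VR-arm drop-out to symptoms. Higher values of k would exceed the planned allowance.

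**Conclusion.** The point holds in limited form. Under the plan as written, participants who permanently discontinue VR because of symptoms are not asked about adverse events, and by this route the objective 10 incidence can be understated but not overstated. Losses for unrelated reasons are a different matter and could move the figure either way.

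The direction follows from the text; the size does not. With an assumed 10 of 33 affected, the shortfall runs from 0 to 9.6 percentage points as symptom-related discontinuations go from 0 to 4, the upper end of the VR arm's share of planned drop-out.

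This should be fixed because the information cannot be recovered afterwards and the remedy is cheap. It is tempting to treat it as a flaw that undermines the trial, but the Protocol does not support that: the primary outcome, its test and the sample size are untouched, and the incidence is an exploratory, descriptive result. The conflict between 4.3 and 3.2.2 is a separate wording error and adds nothing to the size of the bias.

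**What to change.** 1. Record the symptoms listed in 3.2.2 on a short form after each VR session, including the orientation module, and at any early stop or withdrawal during Phase 2. Amend 3.2, 3.4 and the adverse event row of Table 3 to match.
2. Report the incidence over all participants who started VR, orientation included, and report how many discontinued because of symptoms.
3. State that the exclusion in 3.5 for a missing primary outcome does not apply to the adverse event summary.
4. Reconcile the Table 3 drop-out item on insufficient preparation with the rule in 3.2.2 that such participants are dropped before Phase 3.
5. Separately, reconcile the risk statement in 4.3 with the adverse event list in 3.2.2, and check the participant information for the same wording.

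The cost is one short form per VR session, a slightly wider role for the team member whom 3.6.1 already places in Phase 2, and wording changes. No extra visits or staff are needed.

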### 3.2.1 Randomization

Recruited participants will be randomly assigned to the control or intervention group on an equal basis by gender. Participants will not know their allocation to either group until they have watched the entire introductory video and completed Questionnaire 1. Randomization will be performed using the web-based randomization software Randomizer from MedUni Vienna (38).

### 3.2.2 Control and Intervention

The control group will complete an e-learning course over a two-week period in preparation for the subsequent simulation session, which will teach the same content as the VR simulation software in the intervention group.

Both e-learning and VR have the limitation that manual skills cannot be practiced. The content will therefore focus on procedural processes and guideline adherence in the context of trauma patient care and traumatic cardiac arrest in shock rooms. In addition to basic life support (BLS) and ALS, there will be additional specific learning content (15) such as structured patient assessment (xABCDE approach) and special care strategies for this unique patient population.

The e-learning course will also focus on basic principles of crew resource management (CRM) and related communication skills (15,39), such as closed-loop communication. It has also been shown that cognitive aids such as checklists, flowcharts, or mnemonics can be very helpful to HCPs in such settings, and their use is recommended (20). Accordingly, their use will also be an essential part of this e-learning course.

Once enrolled, all participants randomized to this group will receive access information for the course, which, like the VR training, will be conducted in German and must be completed within 2 weeks.

Participants randomized to the intervention group will learn and practice the exact same content using a VR training environment co-developed by the research team of this study. The developed software with its four TCA scenarios must also be practiced over a period of 2 weeks, which corresponds to the same time and learning effort as the e-learning course.

In order to make the VR training sessions as efficient as possible, it is necessary to provide the participants with an additional orientation module that must be played before the VR training sessions begin. This additional module will take about 20 minutes to play once to familiarize the participants with the technical features of the VR headset and the controllers and to keep their focus on the medical content instead of the technical features. The developed software will be a single-user application with automated agents as a resuscitation team for interaction.

All four virtual intervention group simulations or the entire e-learning course must be completed before entering Phase 3, or the participant will be dropped from the study.

### **VR-related adverse events:**

AEs may occur during the use of VR, especially cybersickness (41). The following symptoms' incidence will be evaluated accordingly:

- Nausea and/or vomiting
- Dizziness
- Headaches
- Eye strain and fatigue (discomfort, blurred vision, reduced visual acuity)
- Physical effects (tripping, falling, and bumping into objects in the real world)

### **3.2.3 Simulation sessions**

The simulation sessions (assessments) in Phase 3 will take place in the simulation rooms of MedUni Vienna. Before beginning the manikin-based simulation scenario, participants will be given time to orient themselves and become familiar with the room and the setting itself, the various functions of the manikin, the equipment, and the medications provided. The positioning of the manikin and the equipment will intentionally be laid out to look as similar as possible to the illustrations provided in the e-learning course and to the VR environment.

Participants act as medical team leaders to complete a standardized trauma scenario, which is not known in advance, in a simulated shock room. However, it is defined that the participants know beforehand that basically all the content of the preparatory courses/simulations in Phase 2 could be of importance in the simulated scenario. Which of these learned and trained skills will be used when, if, and how is entirely up to the participants.

The corresponding assessment scenario, which is identical for both groups, refers to a trauma patient with a developing tension pneumothorax who will always require resuscitation. Such an approach is also consistent with the ALS assessment standards of the so-called CASTesting (cardiac arrest simulation testing) in the ERC provider courses. In this study, however, an additional focus is placed on the care of critically injured trauma patients entering a resuscitation situation in a shock room setting. Because of this additional focus, these scenarios will last for 15 instead of 10 minutes, which is ERC's standard for CASTesting (42).

In order to objectively evaluate the participants' performance, the scenario will be recorded by pre-installed cameras in the simulation room. In addition, all actions will be recorded from the participant's perspective using eye-tracking glasses.

The simulation room provides nearly identical conditions and materials as the real shock room. The high-fidelity manikin used will be controlled in a predefined and standardized manner from the control room by experts on the study team.

The physician being assessed always enters the scenario alone. In this setting, seven people form a team and only the team leader is evaluated. The other six confederates, members of the study team, will

represent one resident in anesthesiology and intensive care, one resident and one specialist in traumatology, two nurses, and a radiology assistant. They will act naturally and only as an emergency/resuscitation team. These team members are not allowed to assist the team leader with medical decisions and are only allowed to perform actions on the team leader's orders.

The scenario used begins in a shock room setting with the patient already transferred from the ambulance rescue stretcher to the shock room table and will already be fully monitored. The patient will already have a small lumen (20G) peripheral venous catheter and will be ventilated with an endotracheal tube. Prior to the start of the scenario, all further information regarding the patient's rescue by the emergency medical service will be provided by the emergency physician to the team leader (participant) on a sheet of paper using the SBAR approach. At this point, the patient is wearing only shorts and there is no external bleeding apparent. Immediately after the start of the scenario, which is defined as the time when the instructor gives a "start" signal, exactly 20 seconds after he/she hands over the aforementioned sheet of paper, the patient's hemodynamic deterioration will be fulminant, leading to cardiac arrest after a predefined time.

For performance assessment, critical actions (Table 1) and protocol deviations (Table 2) were defined according to the ERC guidelines on adult ALS (30) and cardiac arrest in special circumstances (31) and the AWMF guideline on polytrauma and management of critically injured patients (32).

**Table 1.** Critical actions

|    | Critical action                     | Time measurement                                                                           | Notes                                                                                                                                                                                                                                                                                                                                                                                       |
|----|-------------------------------------|--------------------------------------------------------------------------------------------|---------------------------------------------------------------------------------------------------------------------------------------------------------------------------------------------------------------------------------------------------------------------------------------------------------------------------------------------------------------------------------------------|
| #1 | CPR start                           | From the onset of cardiac arrest to the start of chest compressions                        | The defined point for time measurement is when a team member's hands touch the chest to begin chest compressions.                                                                                                                                                                                                                                                                           |
| #2 | Recognition of tension pneumothorax | From the scenario start to recognition of the tension pneumothorax                         | 
The defined point of time measurement is when the team leader fully pronounces one of the key words, or the earliest point of time when the evaluating expert can conclude the diagnosis from other team leader's phrases. These phrases will be documented.
 
Key words: Pneu; Pneumothorax; Spannungspneumothorax; Entlasten; Büllau; Thoraxdrainage; Minithorakotomie
 |
| #3 | Mini-Thoracotomy                    | From the start of CPR (defined as in critical action 1) to performing the mini-thoracotomy | The point at which the scalpel touches the chest to perform the mini-thoracotomy is the defined point for time measurement.                                                                                                                                                                                                                                                                 |

*CPR = cardiopulmonary resuscitation*

Critical actions are defined as actions that, if not performed correctly and in a timely manner, could result in serious harm to the patient in this scenario. As these critical actions build on each other, the primary outcome is defined as critical action #3. The simulation (assessment) session will also not allow to perform a mini-thoracotomy before starting CPR.

The measured times to critical actions #1 and #2 will also be assessed as a secondary outcome.

If the participants do not recognize the underlying cause of the TCA, tension pneumothorax, and therefore do not direct CPR to prioritize and perform a mini-thoracotomy, a simulated specialist in anesthesiology and intensive care will enter the scenario and take over team leadership at exactly 15 minutes. In this case, the scenario will continue for an additional three minutes to achieve ROSC and still provide a positive learning outcome for the participants but will be considered a censored observation for further statistical evaluation.

The purpose of this approach is to ensure that the specific sequence of a TCA, with the increased/earlier focus on ruling out reversible causes and even interrupting chest compressions to treat them, if necessary, is the focus of CPR in these special circumstances.

**Table 2.** Protocol deviations

| Primary assessment |                                                                       |                                                               |
|---------------------------|-----------------------------------------------------------------------|---------------------------------------------------------------|
| c                         | Actively searching for signs of massive internal or external bleeding | Inspection and palpation                                      |
| A/B                       | Check airway/tube placement                                           | Position check (etCO 2 , auscultation)             |
|                           | Check thorax                                                          | Inspection and auscultation (if not already done)             |
|                           | Check respirator settings                                             | Checking the respirator and its settings                      |
|                           | Check jugular veins                                                   | Inspection                                                    |
|                           | spO 2 check                                                | Checking the monitor                                          |
| C                         | Pulse check/heart rate                                                | Checking the pulse and the monitor                            |
|                           | Check of skin color                                                   | Inspection                                                    |
|                           | Check of capillary refill time                                        | Inspection and palpation                                      |
|                           | Check of blood pressure                                               | (Non-)Invasive blood pressure                                 |
|                           | At least one additional big lumen vascular access                     | Intravenous or intraosseous                                   |
| D                         | Pupil check                                                           | Inspection                                                    |
|                           | Re-Evaluation/Anticipation of analgesic medication                    | Check for pain and planning analgesic therapy                 |
|                           | Re-Evaluation/Anticipation of narcotic medication                     | Checking state of consciousness and planning narcotic therapy |
| E                         | Removing clothes                                                      | Cut open or take off                                          |
|                           | Temperature check                                                     | Auricular or esophageal                                       |
|                           |                                                                       |                                                               |

|                                                                           |                                                                                                                                                                                                                                 |
|---------------------------------------------------------------------------|---------------------------------------------------------------------------------------------------------------------------------------------------------------------------------------------------------------------------------|
| Secondary assessment                                               |                                                                                                                                                                                                                                 |
| Full body examination                                                     | Inspection and palpation                                                                                                                                                                                                        |
| POCUS examination (eFAST)                                                 | Order for the conduct of the examination                                                                                                                                                                                        |
| Order for full body computer tomography                                   | Order for the conduct of the examination                                                                                                                                                                                        |
| Advanced life support                                              |                                                                                                                                                                                                                                 |
| CPR Start                                                                 | Initiation of CPR (as defined in critical action #1) within 10 seconds following the onset of cardiac arrest, or within 10 seconds after completing the mini-thoracotomy if this procedure takes precedence over initiating CPR |
| Starting the timer                                                        | Order or initiation by the team leader                                                                                                                                                                                          |
| Select team member for time keeping                                       | Order                                                                                                                                                                                                                           |
| Chest compressions depth                                                  | Order/feedback from the team leader to the team member performing chest compressions. If this feedback is not given, the team member is instructed to deliver inadequate chest compressions                                     |
| Chest compressions rate                                                   | Order/feedback from the team leader to the team member performing chest compressions. If this feedback is not given, the team member is instructed to deliver inadequate chest compressions                                     |
| Exchange of person performing chest compressions every two minutes        | Order/check                                                                                                                                                                                                                     |
| Defibrillator placement                                                   | Order for placement within 10 seconds of the start of chest compressions and in the correct position                                                                                                                            |
| Initial rhythm analysis                                                   | Immediate rhythm analysis after placement of the defibrillator                                                                                                                                                                  |
| Rhythm analysis at correct times                                          | Rhythm checks according to ERC ALS guidelines                                                                                                                                                                                   |
| Rhythm analysis duration                                                  | No rhythm analysis lasts longer than 5 seconds                                                                                                                                                                                  |
| Correct recognition of all rhythm analysis                                | All rhythm analyses must be interpreted correctly (shockable, non-shockable, ROSC)                                                                                                                                              |
